### Data management

2.10

Data will be collected by 2 independent trained research assistants using Microsoft Excel. Final data of research data after completion will be collected. A formal data monitoring committee will not be required for the reason the risk is minimal. Independent investigators will monitor the data periodically.

### Statistical analysis

2.11

All data collected during the study will input into SPSS 21.0 statistical software for statistical analysis. Among them, the counting data are expressed in the form of number of individuals and percentage (%). The measurements are expressed in the form of mean and standard deviation (X ± S), and processed by non-parametric test or paired *t* test of 2 related samples. In the statistical results, if *P* < .01, there was a significant difference in the cue data, if *P* > .01, there was no significant difference in the cue data.

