### Study design

2.1

This study will be a single-blinded, randomized, and Diclofenac Sodium Sustained Release Capsules controlled trial. It will be performed at Gansu Provincial Hospital of Traditional Chinese Medicine, Lanzhou, China. The project was evaluated and approved by the Research Ethics Committee of Gansu Provincial Hospital of Traditional Chinese Medicine (Ethical batch No. FJ/04-IRB/C/018-V3.0, Ethics Review Adoption Form places in the Supplemental Digital Content). We planned to begin recruiting patients from July 2019, Patients with stage I, II, and III knee osteoarthritis will be recruited. In this study, there will be 8 investigators. Including 1 chief orthopedic physician, 5 orthopedic physicians, 2 outcome assessors. Five orthopedic physicians will recruit patients. The included patients should meet the inclusion criteria and will introduce the patient to the trial process. The 5 orthopedic physicians will also tell the participants possible benefits and risks.

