### Randomization and allocation concealment

2.5

Sixty patients will be divided into Yuanhu Zhitong dropping pills and Diclofenac Sodium Sustained Release Capsules groups with a ratio of 1:1, random number table will be used for divide the groups. Only the chief orthopedic physicians will be allowed to know the differences of the groups.

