#### Primary outcomes pain^[18,19]^

2.8.1

When the patient takes the medicine, it will be recorded as the first day. Patients will mark on a 100 mm visual analogue scale to assess the pain of their knee (from no pain to severe). At the end of 1, 2, 3, and 4 week, patients themselves and the assessors will record it.

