##### Knee function and patient satisfaction

2.8.2.1

Knee function will be measured The Western Ontario and McMaster Universities Osteoarthritis Index (WOMAC),^[20,21]^ patients themselves and the assessors will also record it at the end of 1, 2, 3, and 4 week. We will record the patient satisfaction at the time their treatment period is finished. A questionnaire will be applied. The questionnaire will be divided into 4 stages, including very satisfied, satisfied, just like, and not satisfied. Patients will fill in the questionnaire by themselves.

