## Discussion

4

The results showed that the Yuanhu Zhitong Drop Pill group was superior to the Western medicine group in terms of VAS scores, WOMAC scale assessment results, patient satisfaction, and gastrointestinal symptoms assessment scale (GSRS scale),^[22]^*P* < .05, adverse reactions. The number of cases was significantly less than that of the western medicine group. This shows that Yuanhu Zhitong drop pills can effectively relieve limb pain without side effects, can improve the quality of life of patients, and has a significant effect.

In recent years, with the continuous development of traditional Chinese medicine research, it has achieved significant results in the treatment of knee osteoarthritis. At the same time, with its unique advantages such as multiple targets for therapeutic effects and low toxic and side effects, it has obtained a large number of patients and doctors. There are still many deficiencies in the research of traditional Chinese medicine for knee osteoarthritis. There are some limitations with this study. First, the sample size of this study is small and it is a single-center randomized controlled study. Second, patients using VAS scores are too subjective. Third, a large number of clinical studies lack long-term efficacy. The safety of the drug need long time to observe.

Therefore, large-scale randomized double-blind controlled experiments should be carried out in future clinical research to strive for innovative and prospective related studies with rich center points and large sample sizes. In conclusion, we hope that the results of this study can provide new evidence for the treatment of early knee osteoarthritis pain with traditional Chinese medicine.

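### Section 2.11 tests the measurements with methods for related samples, although the trial compares two independent randomised groups

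*Protocol article*

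**What the plan says.** Tests are named in one place only, section 2.11 (Statistical analysis) of the protocol article. Measurements are summarised by mean and standard deviation and then "processed by non-parametric test or paired *t* test of 2 related samples", with significance declared at P < .01.

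The design is set out in sections 2.1 and 2.5. Section 2.1 states: "This study will be a single-blinded, randomized, and Diclofenac Sodium Sustained Release Capsules controlled trial". Section 2.5 states: "Sixty patients will be divided into Yuanhu Zhitong dropping pills and Diclofenac Sodium Sustained Release Capsules groups with a ratio of 1:1", and adds that a "random number table will be used for divide the groups". Neither section mentions matched pairs or crossover.

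The primary outcome (section 2.8.1) is pain: "Patients will mark on a 100 mm visual analogue scale to assess the pain of their knee". On timing: "At the end of 1, 2, 3, and 4 week, patients themselves and the assessors will record it". WOMAC follows the same weekly schedule (section 2.8.2.1).

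The inference is between groups. The Discussion words it as "the Yuanhu Zhitong Drop Pill group was superior to the Western medicine group in terms of VAS scores", and extends it to WOMAC and other outcomes.

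**The concern.** The two arms contain different, unmatched patients, so they are independent samples. The only related samples in this design are repeated measurements on the same patient. A paired t test, or its non-parametric counterpart, applied to those measurements asks whether pain changed over time within one arm. That change combines the drug effect with natural course, expectation and regression to the mean, the last being likely because patients enter on a VAS window (section 2.2). Randomisation removes these shared components only when the arms are compared directly.

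At stake is the primary comparison. As written, no named procedure yields an estimate, confidence interval or test of the difference between the pills and diclofenac on VAS or WOMAC, so a superiority statement on either would have no planned test behind it.

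**Working it through.** **1. Design against test (no arithmetic needed).**

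- Units: 60 different patients, 30 per arm, allocated by random number table (sections 2.4 and 2.5).
- Pairing across arms: none is created by the allocation, so a pill patient has no partner in the diclofenac arm.
- Pairing within patients: weekly VAS and WOMAC (sections 2.8.1 and 2.8.2.1).
- Consequence: a paired test can be applied only within an arm. Its target is the mean change in that arm, not the difference between arms.
- Other tests: the article names no independent-samples t test, Mann-Whitney test, ANCOVA or mixed model.

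**2. The plan's own figure.** Section 2.4 goes from 25 to 30 per group for 20% loss: 25 × 1.2 = 30, which reproduces the stated number. The 25 itself cannot be checked, because no effect size, SD or power is given. Applying the 20% loss to 30 gives 30 × 0.8 = 24 evaluable per arm, used below.

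**3. Illustration: what if within-arm verdicts were set against each other?** The plan does not say this will be done. The calculation shows only why within-arm tests cannot stand in for a between-group test.

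Inputs:
- n = 24 per arm (from section 2.4, as above).
- Two-sided alpha 0.01. The level is from section 2.11; two-sidedness is assumed. The critical value of t with 23 df is 2.807.
- Two treatments with the same true mean change m, from 0 to 20 mm (assumed).
- SD of change s = 14.4, 20 or 25 mm (assumed; the article gives none). The low value is the SD of a uniform spread over the 10 to 60 mm entry window, 50/√12 = 14.4 mm, used only as a reference point.

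Formulas: the noncentrality is m√n/s. The chance p that one arm is significant comes from the noncentral t with 23 df. The chance that exactly one of two independent arms is significant is 2p(1 − p).

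Example, m = 10 and s = 20: noncentrality 10 × √24/20 = 2.449, p = 0.381, and 2 × 0.381 × 0.619 = 0.472.

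| Common mean change | s = 14.4 mm | s = 20 mm | s = 25 mm |
|---|---|---|---|
| 0 mm | 0.02 | 0.02 | 0.02 |
| 5 mm | 0.27 | 0.14 | 0.09 |
| 8 mm | 0.50 | 0.35 | 0.23 |
| 10 mm | 0.40 | 0.47 | 0.35 |
| 12 mm | 0.20 | 0.49 | 0.45 |
| 15 mm | 0.03 | 0.32 | 0.49 |
| 20 mm | 0.00 | 0.05 | 0.25 |

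The maximum of 2p(1 − p) is 0.50, reached when p = 0.5. The range is therefore about 0% to 50%. Where the common change is large relative to its SD, both arms are usually significant (95% of trials at m = 20, s = 20), which says nothing about which drug is better.

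**4. Cross-check by simulation.** With 25 per arm, normal change scores, equal true change in both arms and 40,000 runs, exactly one arm was significant at .01 in these proportions of trials, by true change in SD units:

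- 0: 2%
- 0.4: 37%
- 0.5 and 0.6: 48%
- 0.8: 22%
- 1.0: 4%

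An independent two-sample t test on the same data rejected in about 1% throughout.

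**The case against.** **The wording may be looser than it looks.** The related-samples phrase may qualify only the t test, which would leave an unspecified non-parametric test that could be meant for independent groups. That reading is possible, though less natural. It does not repair the plan: no independent-group test is named on either reading, and the one test that is specific remains the paired t test.

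**The article is condensed and a fuller plan may exist.** This would answer an omission, but section 2.11 positively assigns measurements to a procedure that does not fit the design. A correct analysis plan would contradict it.

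The same objection does succeed against some stronger readings.

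- *Satisfaction and count data.* A reader might infer that these also lack a valid test, since satisfaction is recorded once, at the end of treatment, and counts are only described as number and percentage. But section 2.11 names paired tests for measurements and does not say that the four-category satisfaction item will be tested that way. Tests for these outcomes may be left to a fuller plan, so this is no finding.
- *A false-claim rate near one half.* A reader might take 47% or 49% as the error rate of this trial. Nothing in the article says that a significant arm will be set against a non-significant one, and the figure runs from about 0% to 50% depending on an SD and a mean change that the article does not give.
- *A trial that cannot answer its question.* The randomised weekly data can answer it; only the analysis as written does not.
- *An efficiency gain from ANCOVA.* The saving depends on the correlation between baseline and week 4, which is not stated: 1/(1 − 0.5²) = 1.33 at 0.5, but 1/(1 − 0.3²) = 1.10 at 0.3. It is not evidence of the error and plays no part in the conclusion.

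**Conclusion.** Wrong as written. Section 2.11 assigns VAS and WOMAC to within-patient tests, while sections 2.1 and 2.5 set up two independent groups and the Discussion draws a between-group conclusion. This rests on the text alone and needs no assumption about effect size or SD.

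The 0% to 50% range is illustrative. It assumes normal change scores, 24 evaluable per arm, two-sided alpha 0.01, SD of change 14.4 to 25 mm, a common mean change of 0 to 20 mm, and a comparison of verdicts that the plan does not announce. The point must be fixed because it affects the primary comparison.

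**What to change.** Replace the sentence on measurements in section 2.11 with:

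> The primary comparison is the between-group difference in week-4 VAS by ANCOVA with treatment and baseline VAS, reported with its confidence interval; WOMAC is analysed the same way; within-group paired tests are descriptive only.

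An independent-samples comparison would also cure the mismatch. ANCOVA is a sound choice because VAS is already measured at entry for eligibility (section 2.2).

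The cost is a change of wording. SPSS, the software already named, runs the analysis. For VAS, state that the entry value serves as baseline. For WOMAC, confirm that a pre-treatment value is recorded, since section 2.8.2.1 lists only weeks 1 to 4; a before-after paired test would need that value too.

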### Sample size calculation

2.4

Preliminary estimates put the number of cases in each group at 25. Considering the influence of shedding and elimination (20%), the overall sample size was set as 60 cases, 30 cases in the experimental group and 30 cases in the control group.

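### The named test for VAS and WOMAC compares two readings within a patient, so it gives no contrast between the arms and discards the partial weekly follow-up of patients who leave

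*Protocol article*

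**What the plan says.** - **Method.** Section 2.11, Statistical analysis, has measurements summarised by mean and SD and "processed by non-parametric test or paired" t test, the latter for two related samples. It names no other test for VAS or WOMAC.
- **Schedule.** Section 2.8.1 has the primary outcome, pain on a 100 mm VAS, recorded "At the end of 1, 2, 3, and 4 week". Section 2.8.2.1 puts WOMAC on the same four weeks. No single week is named as primary.
- **Design.** Section 2.5 randomises 60 patients 1:1 to two parallel drug groups.
- **Expected loss.** Section 2.4 states: "Preliminary estimates put the number of cases in each group at 25". It then continues: "Considering the influence of shedding and elimination (20%), the overall sample size was set as 60 cases", that is "30 cases in the experimental group and 30 cases in the control group".

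**The concern.** The stated method does not fit the stated design in two ways.

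First, the trial asks whether one drug relieves pain better than the other. A related-samples test asks whether patients changed between two readings. Run once in each arm, it gives two within-arm p-values and no estimate of the difference between arms.

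Second, the test needs both readings of a pair. A patient who leaves after week 1, 2 or 3 drops out of any pair ending at week 4, although one to three on-treatment readings exist.

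The article itself makes outcome-related, unequal loss plausible. The Introduction says that side effects made some patients stop anti-inflammatory drugs, and only the control arm receives one. Section 2.7 lists too little therapeutic effect among the reasons for discontinuation, although it does not say whether this applies to a patient or to the whole study. If poor responders leave more often from one arm, that arm's completers look better than the patients who were randomised to it.

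**Working it through.** **1. The plan's own figure.** 25 × 1.2 = 30 per arm, 60 in total, as stated. (Dividing by the retained fraction would give 25 / 0.8 = 31.25, so 32 per arm; that is a separate matter.) If the whole 20% became missing week-4 readings, complete pairs would number 30 × 0.8 = 24 per arm, one below the 25 planned.

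**2. Inputs for the bias.** The article gives no VAS SD, no correlation between weeks, and no split of the loss by arm or reason. All of these are assumptions:
- SD 10 to 20 mm. The only hint is the entry range of 10 to 60 mm; a uniform spread over it would give 50/√12 = 14.4 mm.
- Correlation ρ of 0.5 to 0.7 between the earlier reading and week 4.
- Loss of 10% v 30%, that is 3 and 9 of 30, so 12 of 60 = 20% overall.
- Leaving depends on the earlier VAS, either through a logistic slope of 0.5, 1 or 2 log-odds per SD or through a hard cut-off.

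**3. Formula.** Bias in completers' mean week-4 VAS within an arm = ρ × SD × s, where s is the shift, in SD units, of the earlier VAS among those who stay. For a hard cut-off with loss d, s = −φ(z₁₋d)/(1−d). The between-arm bias is ρ × SD × (s at 30% − s at 10%).

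| Leaving rule | s, 10% loss | s, 30% loss | Difference | SD 10, ρ 0.5 | SD 15, ρ 0.7 | SD 20, ρ 0.7 |
|---|---|---|---|---|---|---|
| slope 0.5 | −0.0488 | −0.1427 | −0.0939 | −0.47 mm | −0.99 mm | −1.31 mm |
| slope 1 | −0.0908 | −0.2528 | −0.1620 | −0.81 mm | −1.70 mm | −2.27 mm |
| slope 2 | −0.1427 | −0.3749 | −0.2322 | −1.16 mm | −2.44 mm | −3.25 mm |
| hard cut-off | −0.1950 | −0.4967 | −0.3017 | −1.51 mm | −3.17 mm | −4.22 mm |

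A negative sign means that the arm losing more patients looks better than it is. The range is about 0.5 to 4.2 mm.

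**4. Where the bias is zero or larger.** If loss is random, s = 0 in both arms. If 20% leave each arm by the same rule, the two shifts cancel and the between-arm bias is 0 mm. If 20% leave each arm but by opposite rules, the bias runs from about 1 mm (SD 10, ρ 0.5, slope 0.5) to 9.8 mm (SD 20, ρ 0.7, hard cut-off).

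**5. Change scores.** The formula in step 3 concerns the week-4 level, whereas a paired test uses a change. A large-sample simulation therefore let patients leave after weeks 1, 2 or 3 according to lack of improvement so far (slope 1), with no true difference and total loss of 10% v 30%. The completers' between-arm difference in change was −1.4 to −3.0 mm for SD 10 to 20 with AR(1) correlation 0.7, and −0.9 to −1.7 mm with exchangeable correlation 0.6. A likelihood estimate using all the weekly values stayed within 0.1 mm of zero. These results lie inside the range of step 3.

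**6. When leaving depends on the unseen value.** With SD 15, ρ 0.7, slope 1 and 30% v 10% loss driven by the week-4 value itself, completers are biased by −2.44 mm and the likelihood estimate by −1.36 mm. So (2.44 − 1.36)/2.44 = 44% is removed. With 20% loss in opposite directions the figures are −5.20 and −2.82 mm, so 46% is removed.

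**The case against.** **A missing-data rule belongs in the full protocol or SAP, which are not shown.** That stands, and the absence of such a rule is not the point here. The point is the test that the article does name.

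**The phrase about related samples may qualify only the t test, leaving the non-parametric option open to an unpaired test.** The sentence can be read so. The t test would still be within-patient, no between-arm test would be identified, and a rank test at one week would still lose everyone missing that week.

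**The size is undocumented.** This stands in full. A reader might infer a definite bias of some 2 to 4 mm. The article gives no SD, correlation or split of loss by arm, and the bias is zero under loss that acts alike in both arms. Nor does the article state an arm comparison to which a bias could attach; the range describes what would follow if one were built from complete pairs.

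**The 20% is not all lost follow-up.** This also stands. A reader might take it that a fifth of patients will have early readings but no week 4. The allowance covers elimination as well, some may leave before week 1, and those who leave later still form pairs for the weeks they attended.

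**Data management.** A reader might infer from "Final data of research data after completion will be collected" that weekly values will go unentered. The text does not say so: the same section has the data monitored periodically, and section 2.11 has all data collected during the study entered for analysis.

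**Conclusion.** The point holds as a mismatch between a stated method and a stated design. The related-samples test cannot estimate the difference between two independent arms, and it wastes the weekly readings of patients who leave; neither statement needs an assumption. The bias is conditional. It is roughly 0.5 to 4 mm on the 100 mm scale for loss of about 10% v 30% that follows earlier response, given SD 10 to 20 mm and correlation 0.5 to 0.7. It is 0 mm if loss is random or acts alike in both arms. A reader might also infer that a repeated-measures model would remove the bias whatever its cause. It does so only when leaving depends on recorded values; where leaving follows the unrecorded week-4 value, the example above shows a little under half removed. The change is worth making because it also supplies the missing between-arm contrast.

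**What to change.** In section 2.11, replace the related-samples test as the between-arm analysis of VAS and WOMAC with a mixed model for repeated measures on weeks 1 to 4:
- terms for arm, week, arm-by-week and the pre-dose value, with an unstructured covariance;
- every randomised patient with at least one weekly value included;
- the arm contrast, with its confidence interval, read at one week named in advance, for example week 4, the end of treatment.

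Within-arm paired tests may stay as description.

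**Cost.** Mainly analysis wording: the weekly readings are already scheduled, and the MIXED procedure of the named software fits the model. A pre-dose VAS is implied by the entry criterion. The article does not mention a pre-dose WOMAC, so confirm that one is taken. Patients lost before week 1 still contribute nothing. Because leaving may depend on values that were never recorded, report loss by arm, week and reason beside the result.

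### The analysis section declares significance only below .01, but the Discussion attaches P < .05 to a superiority statement, so a result between the two levels has no settled verdict

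*Protocol article*

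**What the plan says.** Protocol article, section 2.11 (Statistical analysis), is the only place that says how a P value becomes a verdict: "if *P* < .01, there was a significant difference in the cue data, if *P* > .01, there was no significant difference". The rule covers the statistical results in general. It sets no separate level for any endpoint and does not say whether the test is one- or two-sided.

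The Discussion (section 4) states: "The results showed that the Yuanhu Zhitong Drop Pill group was superior to the Western medicine group in terms of VAS scores". The list continues with WOMAC, patient satisfaction and a further scale, and closes with the level: "gastrointestinal symptoms assessment scale (GSRS scale),^[22]^*P* < .05, adverse reactions".

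Section 2.4 (Sample size calculation) cannot settle which level was intended. It says "Preliminary estimates put the number of cases in each group at 25", adds a 20% allowance for losses to reach 30 per group, and gives no significance level, power, effect size or SD.

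**The concern.** The significance level has to be fixed before the data are seen, because it turns the primary comparison into a conclusion. Here the rule names .01, and the only superiority statement in the article rests on .05. For a P value between them, an author could cite section 2.11 for no significant difference or point to the Discussion's level for superiority. Whoever writes the report could pick the favourable reading once the result is known.

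The level also determines what 60 patients can show. The effect detectable with 80% power differs by about 0.2 SD between the two levels, so the article leaves open how sensitive the trial is meant to be.

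**Working it through.** **1. The two levels side by side**

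| P value | Section 2.11 | Level cited in the Discussion |
|---|---|---|
| below .01 | significant | met |
| between .01 and .05 | no significant difference | met |
| above .05 | no significant difference | not met |

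Only the middle row is in conflict.

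**2. Can the sample size show which level was meant?** The stated 30 per group follows from 25 × 1.2 = 30. (Dividing instead, 25 / 0.8 = 31.25, would round up to 32.) The 25 itself cannot be rederived, because section 2.4 gives no inputs. It happens to match d = 0.8 at two-sided .05 with 80% power under the normal approximation, but that effect size is an assumption and does not show that .05 was used.

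**3. Size of the conflicting zone.** Inputs: n = 25 per arm (section 2.4). Assumptions: a two-sided, two-sample t test with 2n − 2 = 48 degrees of freedom. Section 2.11 itself names a paired t test or a non-parametric test for two related samples. I use the two-sample test because the question is the difference between two randomised arms.

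The smallest observed standardised difference that reaches level α is t(1 − α/2, 48) × √(2/n), with √(2/25) = 0.2828.

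- α = .05: 2.0106 × 0.2828 = 0.57 SD
- α = .01: 2.6822 × 0.2828 = 0.76 SD

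The documents give no SD for the VAS. Under assumed SDs the zone is:

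- SD 15 mm: about 8.5 to 11.4 mm
- SD 20 mm: about 11.4 to 15.2 mm
- SD 25 mm: about 14.2 to 19.0 mm

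Section 2.2 admits patients with VAS between 10 and 60 mm, so differences of this size are possible. With all 30 per arm evaluable (58 degrees of freedom) the zone is 2.0017 × √(2/30) = 0.52 SD to 2.6633 × √(2/30) = 0.69 SD.

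**4. Chance of landing in the zone.** This is power at .05 minus power at .01 (noncentral t, noncentrality d × √(n/2), 25 per arm), over assumed true effects d:

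| d | Power at .05 | Power at .01 | Chance of .01 < P < .05 |
|---|---|---|---|
| 0.5 | 41% | 19% | 22% |
| 0.6 | 55% | 30% | 25% |
| 0.7 | 68% | 43% | 25% |
| 0.8 | 79% | 56% | 23% |
| 0.9 | 88% | 69% | 19% |
| 1.0 | 93% | 80% | 14% |

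**5. Detectable effect.** With 25 per arm, 80% power is reached at d = 0.81 for .05 and d = 1.00 for .01. At d = 0.81 the power under .01 is 57%. Under .01, 50% power is reached at about d = 0.75.

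**The case against.** The best defence is that the article contains only one decision rule. In the Discussion, P < .05 sits beside a reported result and is not worded as a threshold, and a P value reported as below .05 may also be below .01. This stands: the conflict is confined to values between .01 and .05, and the article does not set out two formal rules. But .05 is the only level given in support of the superiority wording, and section 2.11 would not allow that wording in the middle zone.

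A second defence is that .01 is merely cautious. A strict level is legitimate. The defect is that it is not used consistently.

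Three stronger readings are tempting, and the documents do not carry them.

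- A reader might infer that a result above .01 is meant to be presented as equal efficacy to diclofenac. No section claims equivalence or non-inferiority, and the Discussion claims superiority. The absence of a margin is therefore not an error here.
- A reader might infer that under .01 the trial will probably miss any real difference. That holds only for true effects below about 0.75 SD. At 0.81 SD, significance is the likelier outcome, and 1.0 SD is the 80%-power point, not a limit of detection.
- A reader might infer that section 2.4 was built on .05. It states no level.

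**Conclusion.** The inconsistency is real and narrow. The article's only decision rule uses .01, its only superiority statement cites .05, and no text reconciles them. That the levels differ needs no calculation.

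Its practical size does rest on assumptions: 25 evaluable per arm, a two-sided two-sample t test in place of the paired or non-parametric test named in section 2.11, and assumed true effects of 0.5 to 1.0 SD. Under these, observed differences of about 0.57 to 0.76 SD receive opposite readings, with a chance of about 14% to 25%. The millimetre figures depend further on an assumed SD.

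Matching the two P values would not fully repair the Discussion. Its sentence reports results, whereas section 2.1 describes recruitment and conduct as planned and section 3 says the results will be published. The article does not say where the reported result comes from, so it does not establish whether comparative data had been seen when the levels were written.

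**What to change.** - In section 2.11, state one two-sided significance level, apply it to the between-group comparison of the primary outcome, and use it throughout.
- Remove the superiority sentence with its P < .05 from the Discussion, or explain what data it describes.
- If .01 is kept, state that 25 per arm gives 80% power only for a difference of about 1.0 SD.
- If .05 is chosen, state that 25 per arm gives 80% power for about 0.81 SD, and that the nominal type I error is .05 / .01 = 5 times that of the present rule.
- Report the between-group difference with its confidence interval next to the P value, so that a non-significant result shows how large a difference remains possible.

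The cost is wording only, with no change to patients or visits. The choice of level does have a price: a less favourable detectable difference under .01, or a higher nominal type I error under .05.

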## Introduction

1

Knee osteoarthritis (KOA) is a common chronic knee disease, with pain and limited function as the main causes.^[1,2]^ More than 9,000,000 people have been diagnosed with KOA through clinical and imaging methods in USA.^[3]^ In China, 19.4% of the elderly population more than 60 years of age suffer from KOA.^[4,5]^ According to the Bulletin of the World Health Organization, osteoarthritis is predicted to be the fourth leading cause of disability by 2020.^[6]^ Patients often have symptoms such as pain and dysactivity, which limits the mobility of patients, cause psychosocial problems such as low self-efficacy and depression, and decreases the quality of life.^[7,8]^ The current therapeutic for KOA were mainly aimed to reducing pain and improvement of joint mobility.^[9,10]^

According to the recent guidelines, knee replacement surgery was the only effective pain management approach for the end-stage KOA.^[11,12]^ For the non-surgical treatment of KOA, pharmacological, non-pharmacological and alternative treatments were widely applied in the clinical practice.^[13]^ Among them pharmacologic treatments were the mostly widely adopted. For example acetaminophen, topical treatment, nonsteroidal, anti-inflammatory drugs (NSAIDs), COX-2 inhibitors, opioids and intra-articular cartilage-protective agents.^[14]^ However, long time taking anti-inflammatory drugs was associated with serious adverse reactions, such as digestive and renal impairment.^[15]^ A number of patients had to stop taking drugs for the side effects. Most patients are unwilling to receive routine treatment due to side effects, contraindications, and unsatisfactory relief of symptoms.^[16]^ while not all the patients are the ideal surgical candidates, some patients afraid of operation. Therefore non-invasive, safe and effective treatment options are in great demand for those patients to improve symptoms.

Chinese medicine has been used to manage osteoarthropathy for thousands of years. Yuanhu Zhitong dropping pills were also applied for treat KOA. However its efficacy and security has not been reported in the literature. The purpose of this study is to assess the efficacy and security of Yuanhu Zhitong dropping pills for KOA, a large sample size and a reliable blind method will be used to draw a reliable conclusion.

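### The Discussion infers that the pills have no side effects from fewer adverse reactions than on diclofenac, which does not follow and which 30 patients per arm could not show

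*Protocol article*

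**What the plan says.** The Introduction sets two aims: "The purpose of this study is to assess the efficacy and security of Yuanhu Zhitong dropping pills for KOA". Section 2.4 (Sample size calculation) starts from 25 patients per group and, after a 20% allowance for losses, arrives at "30 cases in the experimental group and 30 cases in the control group". Treatment lasts 4 weeks in both arms (Sections 2.3.1 and 2.3.2).

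Section 2.9 (adverse events) has all adverse events recorded. It lists reactions by body system, including rash, dizziness, nausea and palpitations, and attributes them to both study drugs.

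Section 2.11 describes counts by number and percentage, attaches its named tests to measurements, and closes with a general convention: P < .01 is a significant difference, and otherwise "there was no significant difference in the cue data".

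The Discussion reports significantly fewer adverse reactions than in the diclofenac group and concludes: "This shows that Yuanhu Zhitong drop pills can effectively relieve limb pain without side effects". Later in the same section it concedes that the sample is small and that the drug's safety needs longer observation.

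**The concern.** The step from the comparison to the conclusion is invalid. A lower count than on diclofenac is a statement about the difference between two arms. A statement that the pills have no side effects concerns the rate in one arm, and the difference does not bound that rate. The Introduction itself says that long use of anti-inflammatory drugs carries serious adverse reactions, so a drug could cause fewer reactions than this comparator and still cause many.

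The conclusion also disagrees with two other statements in the article: the list of reactions given for both drugs, and the caveat about longer observation. At stake is one of the trial's two headline conclusions. Patients and prescribers would read it as an assurance that the data cannot give.

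**Working it through.** **Inputs.** From the article: 30 randomised per arm, 25 per group before the allowance for losses, 20% losses, 4 weeks of treatment. It gives no adverse-event rates or counts, so the counts below are illustrations.

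**The plan's own figure.** 25 × (1 + 0.20) = 30 per arm, or 60 in total, as stated. (Dividing instead, 25 / (1 − 0.20) = 31.25, would give 32 per arm and 64 in total. Nothing below depends on this.) I therefore use n = 30, and n = 25 for evaluable patients.

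**Step 1: can a significant reduction coexist with many side effects?** Take 6/30 on the pills and 15/30 on diclofenac.
- Rates: 6/30 = 20% and 15/30 = 50%.
- Fisher exact test, two-sided: P = .029, significant at the .05 level that the Discussion cites.
- Exact (Clopper-Pearson) two-sided 95% upper limit for 6/30, the 0.975 quantile of Beta(7, 24): 38.6%.

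So one patient in five has a reaction on the pills, and up to about two in five cannot be excluded, while the comparison reads as significantly fewer.

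The same holds at the .01 level of Section 2.11. With 4/30 against 15/30, Fisher P = .0048. The rate on the pills is 4/30 = 13.3%, and its exact upper limit, the 0.975 quantile of Beta(5, 26), is 30.7%.

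**Step 2: could the best possible result support the claim?** With no events in n patients, the exact two-sided 95% upper limit is 1 − 0.025^(1/n).
- n = 30: 1 − 0.025^(1/30) = 11.6%.
- n = 25: 1 − 0.025^(1/25) = 13.7%.

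The chance of seeing no case of a reaction with true rate p is (1 − p)^n.
- p = 5%, n = 30: 0.95^30 = 21%.
- p = 3%, n = 30: 0.97^30 = 40%.

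A clean record in this trial would therefore be compatible with reactions in roughly one patient in nine.

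**Step 3: the article against itself.**

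| Place | What it implies |
|---|---|
| Section 2.9 | Reactions in several body systems are associated with both drugs |
| Discussion, comparison | There were significantly fewer reactions than on diclofenac |
| Discussion, conclusion | The pills have no side effects |
| Discussion, limitations | Small sample; safety needs longer observation |

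The third row does not follow from the second and cannot stand with the first or the fourth.

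**The case against.** **Section 2.11 contains no safety decision rule.** This stands. A reader might infer from "there was no significant difference in the cue data" that a non-significant adverse-event comparison will be taken as equal safety. The document does not say so. The sentence is a general convention, the named tests belong to measurements, and the one safety comparison that appears is a claimed reduction, not a null result. Calculations of how often 30 per arm would miss an excess of harm describe an inference that the article never makes, so I do not rely on them.

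**No margin is owed.** This also stands. A reader might think that a safety margin is missing, but no non-inferiority or equivalence claim on safety is made. Descriptive adverse-event reporting is ordinary in a trial of 60 patients.

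**Intervals may be in a full protocol or analysis plan that is not shown.** Their absence from an article is not in itself an error. But no unseen document repairs a printed absolute claim that no result from 30 patients could support.

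**The article already admits its limits.** It does, but the admission contradicts the claim in the same section and does not correct it.

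**The phrase sits among results that a protocol should not yet report, so removing those would remove it.** In part. The wording would go, but the reasoning from fewer to none would be just as invalid once real data replace it.

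**Conclusion.** The point holds as a fault in the stated safety inference. Fewer events than on diclofenac does not establish an absence of side effects. At this size even zero events leaves a true rate of up to 11.6% open (13.7% with 25 evaluable), and a significant reduction can coexist with a 20% rate and an upper limit of 39%. The claim also contradicts Section 2.9 and the Discussion's own caveat.

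The zero-event limits need only the stated sample size and a two-sided 95% exact interval. The 6/30 and 4/30 examples use assumed counts and show what is possible, not what was observed. The point does not extend to saying that the plan reads P > .01 as equal safety, or that it lacks a safety margin. The change should be made: it affects one of the two stated conclusions at almost no cost.

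**What to change.** - **Discussion:** delete the statement that the pills have no side effects. Once data exist, give the observed rate with its upper limit, restricted to the 4-week treatment period. For example, no events in 30 patients would exclude only rates above about 12%.
- **Section 2.11:** state that the proportion of patients with at least one adverse event will be reported for each arm with an exact 95% confidence interval, and the between-arm risk difference with a 95% interval. State that the safety conclusion will be worded from those limits.
- **Consistency:** bring the safety wording of the Discussion into line with the list in Section 2.9 and with the caveat on longer observation. Reconcile the .05 level cited in the Discussion with the .01 level in Section 2.11.

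The cost is a few sentences and one small table, with no added patients, data or staff. The downside for the sponsor is a less favourable safety statement.
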